### Standard-of-care condition

The UK NHS sites and the Uganda site have dedicated clinics for young people growing up with HIV who have previously been in paediatric care, with peer support and professional psychosocial support available in the Uganda site and in the majority of the UK NHS sites. In these clinics, young people can discuss HIV sharing with their multidisciplinary team, attend with their partner, and have access to a range of other services (e.g., HIV testing, PrEP and condom provision). Standard of care in both countries, however, is for there to be no routine or structured psychosocial intervention to facilitate HIV sharing or sharing decision-making.

### Measures

Information on viral load and CD4 counts, as available, will be collected from clinic records. Scales in English will be translated into Luganda during the intervention development phase and adapted as necessary.

#### Primary outcome measure

**Study recruitment and retention**

The feasibility of the intervention will be assessed in relation to study recruitment, retention and acceptability. Recruitment and retention rates will be calculated for each site and for each condition. In addition, post-intervention rating scales will be administered to assess acceptability for participants in the intervention condition (satisfaction, intention to continue to use, and perceived appropriateness of the intervention) [61].

#### Secondary outcome measures

The range of outcomes reflect the likely diversity of the sample and the potential complexity of relationships between sharing, its predictors and consequences.

**HIV disclosure behaviour**

Self-reported HIV-sharing events will be assessed through recording the frequency of new disclosures (full or partial; first hand or second hand with consent) in the last 6 months to partners, friends and family, and any change in the proportion of social network disclosed to.

For each disclosure, recipient and relationship characteristics, perceived satisfaction with HIV-sharing decision, and the nature of the recipient’s response will be assessed. In addition, for those individuals in a participant’s social network not disclosed to, satisfaction with sharing decisions and disclosure intention will be measured. Any social harms occurring as a result of sharing will be recorded. We will develop this measure with reference to existing relevant measures [62–65]. At the follow-up time point for those in both conditions, we will also ask about whether any disclosure support was sought from professionals or social contacts during the previous 6 months.

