Sharing an HIV status carries a unique challenge for young people with PAH with concerns about revealing their mother’s (and other family members’) HIV status [37]. Negative parental sharing attitudes, including directives to not share, may be internalised [37] with an atmosphere of secrecy and limits to open communication about HIV affecting the young person at home, in their community and in the clinic [38, 39]. The subjective difficulty of sharing one’s HIV status in young people with PAH, particularly in relationships, has been frequently reported, with a fear of rejection, a lack of confidence about sharing (disclosure self-efficacy), and fear of secondary disclosure from the recipient to others cited as barriers to sharing [37, 40–42].

There remain important risks of sharing ones’ HIV status, including the threat of rejection, humiliation, stigma and even violence [25, 43]. However, overall, there may be more potential benefits of sharing ones’ HIV status. Hence, for other groups of people living with HIV, there have been efforts to develop HIV status-sharing interventions. Conserve et al. [34] reviewed interventions promoting HIV sharing to sexual partners. Three of the five studies included in this review (four of which focused on MSM, the other minority women) showed rates or frequencies of HIV sharing that were greater in the intervention condition than the control condition, with small-to-medium effect sizes reported. Kennedy et al. [44] reviewed interventions promoting HIV status sharing to *any* recipient in low- and middle-income countries. Seven of the nine studies where outcomes were reported showed a significantly greater level of HIV sharing in the intervention compared with the control arm, with small-to-medium effects. There are no HIV status-sharing interventions specifically designed for young people with PAH, or young people with HIV more generally [45]. Facilitating sharing is often a small component of multi-component interventions for youth with HIV, but this component is rarely evaluated [46]. A recent systematic review of interventions to improve retention in HIV care and adherence to ART among youth highlighted the need for further development and testing of multi-faceted interventions, to address broader social barriers to adherence and retention [47].

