### Intervention condition

The intervention condition will consist of four sessions (90 min per session) delivered in a mixed group/individual format (three group sessions including seven or eight participants/one individual session); professionally led (therapist one); mixed gender; face-to-face; with peer mentor involvement (therapist two) and follow-up support. These features were preferred by clinic attendees in survey of 57 young people with PAH in the UK [53] and were seen as feasible in a second survey of 16 professionals working with this population in the UK [54].

The intervention will aim to develop motivation and skills for HIV status sharing, increase HIV status sharing self-efficacy, decrease anxiety about HIV sharing and increase satisfaction with HIV status sharing decision-making. Motivational interviewing (MI) and Cognitive behavioural therapy (CBT) will guide the intervention. The intervention will be delivered by two therapists in each country. One will be a health professional (not a mental health specialist). The other will be a peer worker.

The content of the intervention is based on models of HIV disclosure decision-making and HIV disclosure anxiety [55–58] and existing evidence of HIV status-sharing correlates, barriers and facilitators [25, 28, 59]. In particular, disclosure attitudes, normative beliefs, self-efficacy, planning and support are argued to be important proximal determinants of HIV status sharing. These factors are suggested to be influenced by more distal factors: personal values and HIV stigma.

The content of specific sessions will be as follows:

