Session 1—Engaging: ground rules, living with HIV, previous experiences of HIV sharing (and evaluation of these experiences), defining HIV status sharing (as a process), understanding HIV status-sharing anxiety, risks and benefits of disclosure and non-disclosure in specific situations and with different recipients, and values clarification exerciseSession 2—Focusing and evoking: HIV sharing wants and needs, eliciting and reinforcement of personal HIV-sharing decision rules, exploring discrepancy between decision rules/current HIV status sharing and values, and examining evidence for HIV status-sharing anxietySession 3—Developing HIV status-sharing skills: identifying barriers and facilitators to HIV status sharing, responding to others’ reactions to HIV status sharing, HIV sharing strategies; developing HIV-sharing decision (if…then) rules, HIV status-sharing communication skills, use of social support (identifying safe/special people to disclose to), managing HIV status-sharing anxiety (challenging anxious thinking), HIV-sharing hierarchies including level of HIV sharing and level of anxiety about response, setting HIV-sharing goals, and planning to disclose (how, where and when)Session 4—Individual goal setting and planning: personal feedback from assessment; assessing HIV-sharing readiness; goal setting; who, how and when to disclose (action planning, using HIV-sharing decision aid); coping with HIV-sharing consequences over time (coping planning); using pre and post HIV-sharing support for self-disclosure recipient; safer sex skills (including condom use); considering nature of relationship with potential recipient, level of HIV sharing, and method of HIV sharing; ways to minimise risk of adverse outcomes/overcome barriers/respond to adverse responses; accepting possibility of adverse outcomes; and producing a personalised HIV-sharing plan

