We will use role play, modelling, cognitive restructuring and behavioural exposure techniques, with both video material and group discussions integrated with interactive exercises. We will aim to space out the sessions to allow reflection on HIV sharing or actual sharing to take place between sessions. Follow-up emotional, informational and problem-solving support (in the 6 months from baseline to the follow-up data point) from a peer worker will be provided for both young people exposed to the intervention and people whom they have disclosed to. This will involve the use of both phone and online/social media options [60].

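### The stated social-harm item covers only harms that result from sharing, so harm from taking part without any sharing falls outside it (low severity)

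*Protocol article*

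**What the plan says.** The harm item is part of the self-report disclosure measure in the protocol article, Secondary outcome measures, HIV disclosure behaviour: "Any social harms occurring as a result of sharing will be recorded". The same section defines the events that the measure counts as "new disclosures (full or partial; first hand or second hand with consent) in the last 6 months", to partners, friends and family. It adds that for each disclosure "the nature of the recipient’s response will be assessed". The section says that the measure is still to be developed from existing instruments.

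The Intervention condition section describes "three group sessions including seven or eight participants/one individual session". It then adds emotional, informational and problem-solving support from a peer worker until the 6-month assessment, offered to participants and to the people they have told: "This will involve the use of both phone and online/social media options". The Standard-of-care condition section describes neither component.

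The Background lists rejection, humiliation, stigma and violence as risks of sharing, and reports "fear of secondary disclosure from the recipient to others cited as barriers to sharing".

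**The concern.** The item puts a causal judgement ahead of data capture: a social harm is recorded if it is judged to result from sharing. The intervention also creates situations that are not the participant's own sharing. Participants sit with other patients with the same diagnosis in group sessions, and they receive peer-worker contact that other people could see. If a participant's status becomes known that way and harm follows, someone applying the item correctly has no reason to record it.

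At stake is the safety information that a feasibility trial passes on to a full trial. If a harm of this kind occurred, a report that followed the item would not show it, although it came from the format of the intervention.

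**Working it through.** No arithmetic applies. The article gives no harm rate and no expected number of harms. The check sets the item's wording against the routes by which a social harm could arise, and then against the other places where harm might be picked up.

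**Step 1: routes to harm and whether the item covers them**

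| Route | Result of sharing? | Covered by the item? | Arms exposed |
|---|---|---|---|
| Participant tells someone, who reacts badly | Yes | Yes | Both |
| Participant tells someone, who tells others; harm follows | Yes, a consequence of the participant's sharing | Yes | Both |
| Status becomes known through a group member, with no sharing by the participant | No | No | Intervention only |
| Peer-worker message or call is noticed by someone else, with no sharing | No | No | Intervention only |
| Study reminder or tracing message is noticed, with no sharing | No | No | Both |

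The first two rows are the main expected route, since the intervention aims to increase sharing. Both lie inside the item. The third and fourth rows lie outside it and arise in one arm only. The fifth lies outside it in both arms, because the Follow-up measurement section has participants in both conditions contacted by phone or SMS 1 month and 1 week before the visit, and non-attenders are traced the same way.

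**Step 2: what the consent qualifier does**

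The phrase "new disclosures (full or partial; first hand or second hand with consent" limits which second-hand disclosures are counted as sharing events. It is not part of the harm sentence. Harm from onward telling without consent is therefore not excluded by that phrase. What decides the matter is whether the participant shared in the first place.

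**Step 3: other places where such harm might appear**

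- Recipient's response (HIV disclosure behaviour): recorded per disclosure, so there is no record where there was no disclosure.
- Psychological well-being and the negative self-image stigma subscale: not tied to sharing, but they measure a state and do not count events.
- Sub-study interviews: ten participants per country, sampled purposively from both conditions. They could bring such a harm to light but give no count by arm.
- Data management and analysis: the confidentiality exception for risk of serious harm may lead to contact with the clinical team. It is not described as a recorded outcome.

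Some of these could reveal a harm of the third or fourth kind. None counts it as a harm by condition.

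**Step 4: number exposed**

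The planned intervention arm is 94 participants (47 in each country). That is an upper limit on the number exposed to group sessions. The intervention section only hopes for attendance at all four sessions and lets participants move on after missing one. With no rate in the documents, no number affected can be calculated.

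**The case against.** The strongest reply is that this is one item in one measure. A disclosure measure that asks about harms from disclosure is not wrong. The sentence does not say that no other harm is recorded, and the article condenses protocol version 3.5, where general adverse-event procedures would normally be found. This stands as a limit on the point: the absence of an adverse-event section is not a finding, and none is claimed. What remains is that the item the article does state depends on attribution to sharing.

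A second reply is that talking in a group is itself sharing, so a breach by a group member could be read as covered. That reading is possible where the breach repeats what the participant said. It is strained where attendance alone reveals the status, and the events counted in the same section are disclosures to partners, friends and family. Ground rules in Session 1 may prevent breaches, but they do not record them.

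Three stronger readings are tempting, and the documents support none of them:

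- *Any loss of confidentiality without consent is excluded.* It is not. A recipient's onward telling follows from sharing and fits the item.
- *The arms attribute harm differently because Session 4 covers* "accepting possibility of adverse outcomes". The sessions also cover the risks of disclosure and how to minimise and respond to bad reactions, which could raise recognition and reporting. The effect could go either way.
- *Intervention harm is undercounted and the comparison is biased towards safety.* The documents show only that the item can miss some harms. The most direct route to harm is inside it, and message exposure exists in both arms.

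**Conclusion.** The point holds as a low-severity wording gap. As written, the item leaves out social harm that arises from participation without sharing. Two of the routes to such harm, group sessions and peer-worker contact, exist only in the intervention condition, so the item can miss intervention-specific harm. The size and direction of any resulting bias cannot be derived from the documents.

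The conclusion rests on two assumptions: that the item is used as the article words it, and that no separate recording of participation harms in the full protocol, which is not shown, already closes the gap. If there is such a procedure, the change below reduces to aligning the item with it.

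**What to change.** Reword the item along these lines:

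*Any social harm since baseline will be recorded in both conditions, whether or not the participant shared; the suspected source (own sharing, onward telling by a recipient, group session, study or peer-worker contact, other) is recorded as a separate item.*

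Report all social harms by condition first, and the sharing-linked subset second. For the comparison by condition, use the 6-month assessment: both arms have it at the same interval from baseline, whereas the post-intervention assessment exists only in the intervention arm.

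The subset now planned is kept, so nothing is lost. The cost is a few items in a measure still to be developed, slightly longer administration, and some unrelated harms counted in both arms. If Phase 2 data collection has already begun, the change can be made by amendment.

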**ART adherence**

Biological correlates of ART adherence (most recent viral load and CD4 count, if available) will be collected from participants’ clinical records. Adherence behaviour will be assessed by the CASE adherence index [66], which has been used in Uganda [28]. The CASE adherence index contains three questions relating to difficulty in taking ART medication on time (scored on a scale from 4—never to 1—all of the time), frequency of missed doses (scored on a scale from 1—everyday to 6—never) and time since most recent missed dose (scored on a scale from 1—within the past week to 6—never). Its reliability and validity has been assessed by estimating the degree of sensitivity and specificity to changes in three-day adherence self-report and comparing it to changes in HIV virologic outcomes and CD4 counts across time [66].

**Psychological well-being**

The 6-item psychological domain from the World Health Organisation Quality of Life brief questionnaire (WHOQOL BREF) [67] will be used. This measure has been translated into Luganda with good evidence of reliability and validity [68]. It includes questions on bodily image and appearance, negative feelings, positive feelings, self-esteem, spirituality/religion/personal beliefs, and thinking/concentration, which are answered on a 5-point scale (e.g. from 1—not at all to 5—completely). As well as measuring wellbeing as an outcome of the intervention, this variable may also mediate changes in other outcomes.

**Social support**

The 6-item Social Support Questionnaire Short form (SSQ6) [69] will be used. For each of the 6 items (e.g. Whom can you really count on to help you feel more relaxed when you are under pressure or tense?), respondents indicate the number of people available to provide support and then rate the overall level of satisfaction with the support given in each of the areas from 6—very satisfied to 1—very dissatisfied. A longer form of this measure has been used with young people living with HIV in Uganda [70]. As well as measuring social support as an outcome of the intervention, this variable may also mediate changes in other outcomes.

**Hope**

The 6-item State Hope Scale will be used [71]. The State Hope Scale offers a brief, internally consistent, and valid self-report measure of ongoing goal-directed thinking [71]. It includes items such as “There are lots of ways around any problem that I am facing now”, and is scored on an 8-point Likert scale from 1 (definitely true) to 8 (definitely false).

**Sexual outcomes**

The frequency and rate of unprotected sexual intercourse will be calculated for casual and regular partners with self-report data. Pregnancy, perceived partner status and PrEP use will also be recorded.

**Decisional conflict scale**

The 4-item decisional conflict scale will be used in relation to decisions to share [72]. The four items are the following: feeling uncertain (**S**ure of myself), feeling informed (**U**nderstand information), feeling clear about values (**R**isk-benefit ratio), and feeling supported in decision making (**E**ncouragement). A response of yes scores 1 and a response of no scores 0; a score of < 4 is a positive result for decisional conflict. The internal consistency of the scale has been shown to be moderate in English-speaking treatment-option patients [72], and the scale has shown adequate psychometric properties in a primary care population with a low prevalence of clinically significant decisional conflict [73].

#### Measurement of hypothesised mediators

**HIV disclosure cognitions and affect**

We will translate and adapt the 18-item HIV disclosure cognitions and affect scale, which has shown good preliminary evidence of reliability and validity in adolescents with PAH [74]. This scale contains three subscales representing negative disclosure attitudes and feelings, disclosure self-efficacy and positive disclosure attitudes and feelings. An example item is, “I am worried they will tell others”. Items are scored on a 5-point Likert scale from strongly disagree to strongly agree. We will develop an HIV disclosure intention item from existing measures [25, 75].

**HIV disclosure planning**

HIV disclosure planning will be assessed by asking two questions relating to action and coping planning. These questions will be adapted from questions used in the study with adolescents with PAH in the UK, from which a novel way of coding HIV status-sharing planning was developed [76].

**ART adherence self-efficacy**

The 14-item behavioural skills subscale of the Life Windows Adherence Questionnaire [77] will be used. This has shown good reliability in different contexts, including in sub-Saharan Africa [78–80]. An example item is, “How hard or easy is it for you to remember to take your HIV medications?”. Response options are 1 (cannot do at all) to 5 (certain you can do).

**HIV stigma**

The three-item negative self-image subscale from the short form of the HIV stigma scale will be used [81]. This has shown evidence of good reliability. An example item is “I feel I’m not as good a person as others because I have HIV”, and responses are on a 4-point Likert scale, ranging from strongly disagree (1) to strongly agree (4).

#### Measurement of background variables

**Previous HIV disclosure**

In addition to recording individual disclosure events in the previous 6 months (above), and the proportion of friends, family and partners disclosed to [63–65], participants will be asked about lifetime HIV-sharing frequency.

**Personal values**

The 24-item Agentic and Communal Value Scale (ACV) will be used [82]. The 24 items include 12 Agency items (e.g. wealth, pleasure, ambition) and 12 Communion items (e.g. forgiveness, trust, politeness) which are rated in terms of the relative importance of each value as “a guiding principle in my life” from not important to me (1) to highly important to me (9). The measure has been used with young adults [83, 84], including those with PAH [85] and has evidence of good reliability.

**Demographic and clinical variables**

Demographic variables (current age, ethnicity, gender, parental loss, relationship status, substance use, pregnancy, housing, location, living situation, education/occupation, income/socio-economic status, sexuality) and clinical variables (age at paediatric HIV disclosure, previous psychosocial interventions, clinic, clinic attendance, regimen, side effects, comorbid health conditions) will be assessed. We will record whether psychosocial support has been offered to the participants over the course of the study in both countries and the nature of any discussions about HIV sharing in standard care. This information will be obtained from participants (during the follow-up assessment) and clinic staff (using standard-of-care monitoring forms).

